#### **VI-2. Screen Failures**

After the screening evaluations have been completed, the investigator or his/her designee is to review the inclusion/exclusion criteria and determine the subject's eligibility for the study. Only the reason for ineligibility will be collected on screen failures. Subjects who are found to be ineligible will be told the reason for ineligibility.

#### **VI-3. Baseline/ Follow-up**

Baseline and follow-up assessments will be organised on Days 1 pre-treatment, 3, 14, 28, 90 and 180 (Table 3). Patients will complete a patient questionnaire and will be contacted by phone. Participants randomised to standard care, or whose care allows it, will have blood samples taken in a health clinic or at home and any follow-up blood, respiratory or saliva samples will be self-sampled or performed by a care nurse.

**Table 3: Table of assessments**

| Day
+/- window (days)                             | Screening
Up to 7
days prior
to D1 | Baseline       | D3
+ 2      | D 14
± 2    | D 28
± 2    | D X 
Hospitalization/O 2 + 2 | D90
± 7  | D 180
± 14  |
|------------------------------------------------------|---------------------------------------------|----------------|----------------|----------------|----------------|--------------------------------------------------------|-------------|----------------|
| Name of visit                                 |                                             | D1      | FU 1    | FU2     | FU 3    | Hospitalization                                 | FU 4 | FU 5    |
| Eligibility criteria                                 | X                                           |                |                |                |                |                                                        |             |                |
| Informed consent                                     | X                                           |                |                |                |                |                                                        |             |                |
| Review SARS-CoV-2 results                            | X                                           |                |                |                |                |                                                        |             |                |
| Review ABO group results                             | X                                           |                |                |                |                |                                                        |             |                |
| Study intervention                            |                                             |                |                |                |                |                                                        |             |                |
| Randomization                                        |                                             | X  |                |                |                |                                                        |             |                |
| CCP administration (only in
treatment arm)        |                                             | X              |                |                |                |                                                        |             |                |
| Study procedures                              |                                             |                |                |                |                |                                                        |             |                |
| Demographics and Medical History                     | X                                           |                |                |                |                |                                                        |             |                |
| Examination / Vital signs                            |                                             | X              |                |                |                | X                                                      |             |                |
| Symptom recording                                    | X                                           | X              | X              | X              | X              | X                                                      |             |                |
| Vital status                                         |                                             | X              |                |                | X              | X                                                      | X           | X              |
| Concomitant medications                              | X                                           | X              | X              | X              | X              | X                                                      |             |                |
| Hospitalisation/ITU                                  |                                             | X              | X              | X              | X              | X                                                      |             |                |
| Ventilation mode                                     |                                             |                |                | X              | X              | X                                                      |             |                |
| Oxygenation                                          |                                             |                |                | X              | X              | X                                                      |             |                |
| Clinical Progression Scale                           |                                             | X              | X              | X              | X              | X                                                      |             |                |
| QoL and long COVID
Questionnaires                 |                                             | X              |                |                | X              |                                                        |             | X              |
| Adverse event recording                              |                                             | X              | X              | X              | X              | X                                                      | X           | X              |
| Laboratory analyses                           |                                             |                |                |                |                |                                                        |             |                |
| SARS CoV 2 RT-PCR in nose and
throat swabs/saliva | X                             | X              | X  | X  | X  | X                                                      |             | X  |

|                                                                                 |                |                  |                |                |                  |                  |  |                  |
|---------------------------------------------------------------------------------|----------------|------------------|----------------|----------------|------------------|------------------|--|------------------|
| SARS CoV 2 sequencing (whole genome sequencing)                                 | X  | X                |                |                | X    | X    |  | X    |
| SARS CoV 2 isolation from nose and throat swab/saliva (cohort 2 only, optional) |                | X  |                |                | X  | X  |  | X  |
| SARS CoV 2 antibody in serum                                                    | X              | X                | X  | X  | X    | X                |  |                  |
| Biochemistry bloods                                                 |                | X                |                | X  |                  | X                |  |                  |
| Haematology bloods                                                  |                | X                |                | X  |                  | X                |  |                  |
| Pregnancy test (in females of childbearing potential only)                      | X              |                  |                |                |                  |                  |  |                  |
| Serum for biobank (optional)                                                    |                | X    |                | X  | X    | X    |  |                  |
| Plasma for biobank (optional)                                                   |                | X    |                | X  | X    | X    |  |                  |
| EDTA sample (for isolation of immune cells) for biobank (optional)              |                | X    |                | X  | X    | X    |  |                  |

 For individuals with no RT PCR or Antigenic test result in the preceding 7 days

 Cohort 2; in cohort 1 only if the patient's have not been tested negative in the SARS-CoV-2 PCR before.

 Urea, Electrolytes, Liver Function Tests (ALT, AST), Creatinine, calcium, phosphate, glucose, C-reactive protein (CRP). LDH, ferritin, IL-6 (optional)

 Full Blood Count (neutrophils/total lymphocyte counts, platelets), Prothrombin, Activated partial thromboplastin time (aPTT), fibrinogen, D dimer, G&S

 Visit "hospitalization" on the day of hospitalization and/or start of supplementary O2 (+ 2 days) (only if this event occurs up to day +28).

 if viral load still sufficient to perform sequencing or virus isolation

 between screening and administration of CCP (D1)

 not mandatory

#### **VI-4. Data recorded**

##### **VI-4-1. Baseline information**

The following information will be recorded on the web-based form by the attending clinician or delegate:

| Data recorded                                                                                                                                     | Source of the data   |
|----------------------------------------------------------------------------------------------------------------------------------------------------------|-----------------------------|
| Medical history including High risk categories/major comorbidity                                                                                         | Patient and medical records |
| Patient details (age, sex...), place of residence, weight, height, BMI, Vital signs                                                                      | Medical records             |
| SARS-CoV-2 vaccination (dates, type of vaccine)(cohort 2 patients)                                                                                       | Patient and medical records |
| COVID-19: COVID-19 symptom onset date, Date of SARS-CoV-2 RNA detection, symptoms details, infection history, COVID-19 severity as assessed by WHO score | Patient and medical records |
| Concomitant medication (including use of any other medication to treat COVID-19 as standard of care)                                                     | Patient and medical records |
| ALAMA risk score                                                                                                                                         | Medical records             |
| Biological data                                                                                                                                          | Medical records             |

##### **VI-4-2. Follow up information**

The following information will be ascertained at each visit, as well as at time of death or at 28 days after first randomisation (whichever is sooner):

- Vital status
- Hospitalisation status
- 10-point WHO progression scale
- Oxygen supplementation and/or ventilation
- Use of renal dialysis or haemofiltration
- Documented new major cardiac arrhythmia (including atrial and ventricular arrhythmias)
- Use of any other medications to treat COVID-19
- AE / SAE / SAR / SUSAR

This information will be obtained and entered into the web-based IT system by a member of the hospital clinical or research staff.

Follow-up information is to be collected on all study participants, irrespective of whether or not they complete the scheduled course of allocated study treatment. Study staff will seek follow-up information through various means including medical staff, reviewing information from medical notes, routine healthcare systems, and registries.

## **VII. STUDY PRODUCT**

Details are available in investigator brochure and product circuit.

### **VII-1. Investigational therapeutic**

The investigational medicinal product is composed of two plasma units provided by two COVID-19 convalescent patients, fully compliant with national regulations as detailed in the investigator's brochure.

The first unit of ABO compatible convalescent plasma (200 to 350 ml per unit) will be infused intravenously on study day 1 (as soon as possible after randomisation) and the second on day 1 or day 2. Plasma has been obtained by apheresis from donors who have recovered from COVID-19 infection (at least 14 days after recovery) and have been vaccinated (at least 3 weeks after first dose of vaccine). A combination of both a SARS-CoV-infection and a SARS-CoV-2 vaccination of the donor is required – irrespective of the sequence of infection and vaccination. As far as the availability of CCP units allows, the two plasma units should have been donated by two different convalescents.

### **VII-2. Convalescent plasma collection**

Plasma units are obtained, prepared and delivered in strict observance of the existing rules, as part of the usual activity of the structures.

Briefly, convalescent donors at least 14 days after the symptoms resolution will undergo plasma apheresis. The convalescent donors will undergo standard pre-donation assessment to ensure compliance with current regulations regarding plasma donation including standard microbiological assessment, as well as anti-HLA Ab detection in women with children.

An anti-SARS-Cov-2 spike IgG Ab titre should be performed. Only CCP with a minimum antibody titre as defined in II-6 will be used.

The following information about immunization events will be collected from donors: date of first SARS-CoV-2 infection, SARS-CoV-2 variant (if variant has been identified), date of SARS-CoV-2 vaccinations, and name of vaccine and data of SARS-CoV-2 breakthrough infection (if such an event happened).

### **VII-3. Storage, Handling, Distribution and Stability**

The component should be stored at a core temperature of –25°C or below (storage period in agreement with national regulations). Although a storage temperature below –25°C improves the preservation of labile coagulation factors, lower temperatures increase the fragility of plastic. Particular care must be taken when handling such packs.

The component should be thawed in equipment designed for the purpose, within a vacuum-sealed overwrap bag according to a validated procedure. The optimal temperature at which the component should be thawed is 37°C; temperatures between 35°C and 39°C are acceptable.

Protocols must be in place to ensure that the equipment is cleaned daily and maintained to minimise the risk of bacterial contamination. After thawing, and at the time of administration, the content should be inspected to ensure that no insoluble cryoprecipitate is visible and that the container is intact.

Once thawed, the component must not be refrozen and should be transfused as soon as possible. If a delay is unavoidable, the component may be stored and should be used within 6 hours.

Process for issuing each unit of convalescent plasma is as follows:

- Unit of ABO compatible convalescent plasma should be thawed as per normal blood bank procedures (ABO matched). Preferentially ABO identical units should be used.
- Convalescent plasma should be transferred to the patient following local procedures
- The two units of plasma should be collected from two different donors.

#### **VII-4. Administration**

Two convalescent plasma units of 200 to 350 ml will be transfused i.v. in patients from the CCP arm, on one or two days.

Process for administration of convalescent plasma is as follows:

- All administration bedside transfusion safety checks must be undertaken.
- The donation number, volume transfused, and start and finish date and time of transfusion should be documented.
- Any suspected serious adverse reaction to transfusion must be reported to the transfusion laboratory as well as being reported on trial documentation.

Convalescent plasma will be administered by staff trained to give transfusions of blood components and have been approved to do so per applicable regulation. All participants must be under surveillance during the infusion and should be monitored closely for 2 hours after the infusion. Plasma transfusion per- and post-transfusion surveillance as well as traceability and haemovigilance will be fully compliant with current regulations.

In hospital, CCP will be administered in day units. The exact logistics will vary depending on each hospital's layout. Home transfusion, as well as transfusion in long-term care facilities or in health centers with dedicated personal, will be considered as well.

#### **VII-5. Appearance**

Clear to slightly cloudy, homogeneous liquid, without visible signs of haemolysis, contained in a bag.

#### **VII-6. Justification for dose**

A anti-SARS-CoV-2 IgG dose dependent effect has been observed in several studies. The selection of donors based on their immunization history (infection and vaccination) and the pre-defined minimum concentrations of anti-SARS-CoV-2 antibodies in the CCP units for this trial will provide a standardized high-dose of anti-SARS-CoV-2 antibodies administered in this trial.

#### **VII-7. Authorised medications**

The list of authorised medications is detailed in a dedicated appendix. The trial scientific committee may update this list whenever necessary to ensure that trial participants receive state of the art standard of care at the time of inclusion. Occasions for a review of this list of authorized COVID-19 specific treatments include, but are not limited to, approval of new specific COVID therapeutics or changes in National Guidelines for patient populations that are also eligible for this study.

**An update of this Appendix of Authorized Treatments will not be classified as a Protocol Amendment as long as the above conditions are met.**

#### **VII-8. Discontinuation of study intervention**

Definition: Premature discontinuation of treatment = corresponding to the discontinuation of treatment with the investigational drug.

#### **VII-8-1. Procedures for replacing these people, if applicable**

Not applicable

#### **VII-8-2. Procedures for monitoring these people**

Standard of care

### **VII-9. Participant discontinuation/withdrawal from the study**

If a subject is withdrawn before completing the study, the reason for withdrawal will be entered on the appropriate eCRF. Whenever possible and reasonable, the evaluations that were to be conducted during the final study visit should be performed at the time of premature discontinuation.

It is vital to obtain follow-up data on any subject who terminated because of an AE. In any case, every effort must be made to ensure safety follow-up procedures are completed.

A decision by a participant (or their parent/guardian) that they no longer wish to continue receiving study treatment should not be considered to be a withdrawal of consent for follow-up. However, participants (or their parent/guardian) are free to withdraw consent for some or all aspects of the study at any time if they wish to do so. In accordance with regulatory guidance, de-identified data that have already been collected and incorporated in the study database will continue to be used (and any identifiable data will be destroyed). For participants who lack capacity, if their legal representative withdraws consent for treatment or methods of follow-up then these activities would cease.

### **VII-10. Study discontinuation**

At any time, the investigator as well as the sponsor reserve the right to prematurely interrupt the trial for medical and / or administrative reasons. This will only take place after mutual consultation. The reasons for the stop must be properly documented and the stop of the test must be notified to the competent authorities concerned.

## **VIII. MEASURES TO MINIMISE BIAS**

### **VIII-1. Randomisation**

In addition to receiving usual care, eligible patients will be allocated using a central web-based randomisation service (CleanWeb, Telemedicine Technologies, Boulogne Billancourt, France) available at <https://chrub.tentelemed.com>.

The randomisation service will allocate the treatment based on a pre-specified randomization list generated by the data manager. Separate randomisation lists will be used for each patient population. Randomisation will be performed at a 1:1 ratio, blocked (with randomly varying block sizes of two and four) and stratified by centre. Once randomised, patients are irrevocably enrolled in the study, whether or not they are subsequently found to be eligible or actually receive the allocated treatment. As a consequence, patients should be followed until their last visit, until stopping rules apply or death.

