## **IV. STUDY DESIGN**

### **IV-1. Overall design**

COVIC-19 is a multicentre international, randomised, open-label adaptive superiority phase III trial to evaluate the efficacy and safety of COVID-19 convalescent plasma in the treatment of COVID-19. It is conducted in a harmonized approach in different countries in Europe.

The study is randomizing adult COVID-19 patients to one of two arms (1:1 ratio): standard of care or standard of care and very high neutralizing Ab titre convalescent plasma. Randomization will be stratified by centre and by patient cohort. The control group will receive 'standard care' therapy. Neither blinding nor placebo will be used to avoid unnecessary intravenous access.

Standard of care therapy may include anti-SARS-CoV-2 specific medication listed as authorized in a dedicated appendix. Centres should ensure that medications used as standard of care are used similarly for patients in both treatment arms.

Participating patients will be included in 2 cohorts of vulnerable patients (cohort 1: unvaccinated elderly ( $\geq 70$  years) and younger with comorbidities (cohort 1:  $< 70$  with comorbidities), cohort 2: immunosuppressed patients).

All subjects will undergo a series of efficacy and safety assessments, including laboratory assays. Subjects will be assessed at baseline, and at Days 3, 14, 28, 90 and 180.

Nasopharyngeal swabs (NP) or lower respiratory tract samples will be obtained at D1 (pre-treatment), and at D3, D14, D28 and D180 (and monthly in case of positivity until of clearance) for cohort 2 and on the day of hospitalization (if applicable).

Blood samples will be obtained at D1, D14 and D28 and on the day of hospitalization (if applicable).

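### Small published block sizes (two and four) within centre-by-cohort lists let staff in this open-label trial often infer the next allocation

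*Protocol*

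**What the plan says.** Section VIII-1 of the protocol, under the chapter on minimising bias, fixes the ratio, the block sizes and the stratification in one sentence: "Randomisation will be performed at a 1:1 ratio, blocked (with randomly varying block sizes of two and four) and stratified by centre". The same section adds: "Separate randomisation lists will be used for each patient population". Section IV-1 agrees: "Randomization will be stratified by centre and by patient cohort". Each combination of centre and cohort therefore runs through its own sequence of short blocks.

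Section IV-1 describes a "randomised, open-label adaptive superiority phase III trial" and says: "Neither blinding nor placebo will be used to avoid unnecessary intravenous access". Staff at a centre can thus see which arm each earlier patient received.

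The protocol's protection of the sequence is that "eligible patients will be allocated using a central web-based randomisation service". It gives no probability for choosing a block of two over a block of four, and no number of centres.

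**The concern.** A central web service hides the list, but it cannot stop someone inferring the next entry from the entries already seen. With 1:1 blocks of two and four, every block closes on an even count. An arm that is one behind is therefore likely to come next, and an arm that is two behind is certain to. The reader of the protocol is told the sizes needed for this inference.

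At stake is who gets enrolled, and when. Care teams choose whom to approach, and the attending clinician judges whether symptoms fit COVID-19 (sections V-1 and VI-1). If the expected arm influences those decisions, even without intent, baseline risk can differ between arms. The safeguards elsewhere in the protocol act later. The adjudication panel protects the classification of hospitalisations. The intention-to-treat principle keeps patients in the arm they were assigned to, but does not restore balance lost at enrolment. The primary test is an unadjusted Z-test, and adjustment for prognostic factors is only to be considered (section X-3).

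**Working it through.** The protocol gives no predictability figure to reproduce, so the check derives one.

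**Inputs from the protocol:** ratio 1:1; block sizes 2 and 4 in random order; one list per centre and cohort; allocations visible; 340 patients per cohort in stage 1; interim analysis at 102 patients per cohort.

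**Assumptions, not in the protocol:** probability *w* of a block of two (base case 1/2); 20 centres per cohort, so 340/20 = 17 patients per list, and 102/20 ≈ 5 per list at the interim analysis. The observer knows the sizes and every earlier allocation on that list, and guesses the likelier arm. An allocation counts as predictable if that guess has probability of at least 80%.

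**Second patient.** The arm opposite to the first follows with probability *w* × 1 + (1 − *w*) × 2/3 = 2/3 + *w*/3.
- *w* = 1/2: 5/6 = 83.3%.
- *w* = 1/3: 7/9 = 77.8%, below the threshold.
- The 80% line is reached when *w* is at least 0.40.

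**First five patients, *w* = 1/2.** The probability that each allocation is predictable at 80% or more is:
- patient 1: 0;
- patient 2: 1 (83.3% sure);
- patient 3: 1/2 × 1/3 = 1/6 (a block of four that opened with two alike, so the next is certain);
- patient 4: 1. If the first two were alike, at least the block of four is known and the answer is certain. If they were opposite, the block was a two with probability (1/2)/(5/6) = 0.6, giving 0.6 × 5/6 + 0.4 × 1 = 90%;
- patient 5: 1/2 × 1/2 × 1/3 = 1/12.

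The mean is (0 + 1 + 1/6 + 1 + 1/12)/5 = 2.25/5 = 45%.

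**First five patients, *w* = 1/3.** Patient 2 drops out. Patient 3 gives 2/3 × 1/3 = 2/9, patient 4 gives 1, and patient 5 gives 1/3 × 2/3 × 1/3 = 2/27. The mean is (2/9 + 1 + 2/27)/5 = 26%.

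**Long-run limit, *w* = 1/2.** A block of two holds one predictable allocation. A block of four holds 2 + 1/3. The average is (1 + 7/3)/2 = 5/3 per block. Over a mean block length of 3 this is 5/9 = 55.6%.

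**Lists of 17.** Carrying the same calculation forward, with sizes equally likely unless stated:

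| Blocks | Predictable at ≥80% | Certain | Best guess correct |
|---|---|---|---|
| 2 and 4 | about 52% | 10% | about 71% |
| 2 and 4, *w* = 1/3 | 43% | – | – |
| 2 and 4, *w* = 1/4 | 36% | – | – |
| 4, 6 and 8 | 19% | about 2.5% | 66.5% |

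With no information, a guess is right 50% of the time.

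**The case against.** Several points on the other side have force.

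- **The figures are conditional.** Mixing probability and list size are both assumed. Short lists are plausible, because four countries recruit through hospitals, nursing homes and general practice, and each centre's patients are split over two cohorts. This stands, and is why a range is given. A list with one patient gives no predictability at all.
- **The 80% threshold is favourable to the concern.** It lies just under the 83.3% that follows the first patient of a block. On lists of 17, the share for blocks of two and four is 42% at 85% confidence and 18% at 90%. At 75%, blocks of 4, 6 and 8 still give 37%, against 52%. Overall guessing accuracy improves by only about 4.3 points. This also stands: larger blocks reduce confident predictions much more than they reduce guessing in general.
- **Opportunity to steer is limited.** Transfusion must be possible within 7 days of symptom onset, approaching teams need not follow the allocation sequence, and randomised patients cannot be removed. Baseline characteristics are reported by arm. These limits reduce the opportunity for steering but do not remove it.
- **Small blocks serve balance in small strata, and nothing in the protocol is contradictory here.** True. But the primary Z-test is unstratified and does not rely on balance within centres, so the gain is modest.

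A reader might infer that half of all allocations in this trial are known in advance, or that its results will be biased. The protocol supports neither. The first needs assumptions it does not confirm. The second needs evidence that staff track the sequence and act on it.

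**Conclusion.** The concern holds as a vulnerability. The protocol publishes short blocks within centre-by-cohort lists in a trial where allocations are visible, and central allocation does not prevent the inference. With equally likely sizes and about 17 patients per list, about 52% of allocations are predictable with at least 80% probability and 10% with certainty. The share is about 43% if blocks of two have probability 1/3, and 26% to 45% on lists of five.

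All of these assume an observer who tracks every allocation on the list. They measure what could be predicted. How much bias might follow cannot be derived from the protocol, because it would depend on how often and how strongly enrolment decisions respond to the expected arm. The case for change is that exposure can be lowered cheaply, not that the trial is invalid.

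**What to change.** For allocations not yet made, stop using blocks of two and draw at random from larger sizes, for example 4, 6 and 8. In section VIII-1, keep the statement that allocation is 1:1, blocked and stratified by centre, but take out the sizes and hold them in a randomisation document with restricted access. Patients already randomised are unaffected.

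The cost is a protocol amendment in a multinational trial and regeneration of the unused list entries. Imbalance within small centres will rise slightly. It should not be assumed that the analysis absorbs this: the primary Z-test does not adjust for centre, and the model with a random centre effect is only a sensitivity analysis. Since the primary test does not depend on balance within centres, the price is acceptable.
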